#### Sample Size {14}

Power analysis was conducted using software PASS.15 for the primary outcome (change in salivary cotinine over a year) in Aims 1 and 2. Sampling 16 clusters (buildings) with 4 subjects per cluster (smokers for Aim 1, non-smokers for Aim 2) in each arm, we have 128 subjects per group or 256 in groups with or without a specific type of treatment (e.g. resident endorsement vs. no endorsement, cessation vs. no cessation). We calculated effect size as group mean difference in unit of standard deviation (SD) of the outcome, based on a two-sided test for mean difference between two groups in a cluster-randomized design with power of 80%. To compare groups with and without specific type of treatment, the group size of 256 may detect effect size of 0.283SD, 0.299SD, 0.312SD at significance level alpha = 0.05 for intra-cluster correlation coefficient r = 0.1, 0.15, 0.2, respectively. To compare intervention arms to the control arm, we have 3 comparisons and use conservative Bonferroni adjustment for multiple tests on significance level that alpha = 0.0167 (= 0.05/3). The sample size of 128 subject per arm may detect effect size of 0.472SD, 0.499SD and 0.524SD for r = 0.1, 0.15 and 0.2, respectively, at alpha = 0.0167. To put these numbers in perspective, using mean and SD estimated from a study of smokers in Maryland, an effect size of 0.283SD would correspond to a mean difference in salivary cotinine between the two intervention groups of 55.3 ng/mL with group SD = 195.4 ng/mL for smokers and of 0.19 ng/mL with group SD = 0.672 ng/mL for non-smokers.124 For instance a mean difference in 5 cigarettes smoked per day in the same study was 59.6 ng/mL for smokers.124 In England, following the smoke-free legislation salivary cotinine declined from mean level of 0.36 to 0.07 ng/mL (mean difference 0.29 ng/mL) among non-smokers.125 These findings support that we have sufficient power to estimate the impact of our interventions. The study is powered on an 80% retention rate, which we have achieved in other studies. Reasons for attrition will be tracked; those lost to follow up will be compared to the final sample.

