## Statistical methods

### Statistical Methods For Primary And Secondary Outcomes {20a}

We will conduct intent-to-treat (ITT) and contamination-adjusted intent-to-treat (CA-ITT) analyses to estimate the effects of the smoking relocation/cessation and resident endorsement interventions compared to the standard program implemented by NYCHA (no treatment). CA-ITT analyses will account for unanticipated contamination between trial arms and be completed via two-stage instrumental variables regressions using the original random allocation codes per assigned unit. Preliminary data analysis will include examination of distribution and summary statistics of all variables by intervention groups at each time point. The continuous variables with skewed distribution will be properly transformed, if necessary, to reduce impact of extreme values or improve model fitting. We will use box-plots to examine how distribution of a quantitative variable varies by categories of a categorical variable, and use scatter plots and Spearman correlation coefficient to examine bivariate associations between quantitative variables. Chi-square and Kruskal-Wallis tests will be used to detect group differences in categorical and quantitative baseline variables, respectively. For successful randomization, we expect no difference in the distribution of all baseline variables among the four arms. The baseline variables that differ by intervention groups and are related to outcomes of interest will be controlled in the aim specific models.

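### Single-step Bonferroni for the three arm-versus-control tests is valid, but Holm's step-down would add power for the second and third rejections at the same 5% family-wise error

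*Protocol article*

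**What the plan says.** The section Sample Size {14} plans two kinds of comparison.

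- **With versus without a treatment (factorial).** Here "the group size of 256 may detect effect size of 0.283SD, 0.299SD, 0.312SD at significance level alpha = 0.05", at intra-cluster correlations of 0.1, 0.15 and 0.2. No multiplicity adjustment is applied.
- **Each intervention arm versus control.** The plan states: "we have 3 comparisons and use conservative Bonferroni adjustment for multiple tests on significance level that alpha = 0.0167 (= 0.05/3"). At that level, "The sample size of 128 subject per arm may detect effect size of 0.472SD, 0.499SD and 0.524SD for r = 0.1, 0.15 and 0.2". The calculation is "based on a two-sided test for mean difference between two groups in a cluster-randomized design with power of 80"%.

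Statistical Methods For Primary And Secondary Outcomes {20a} says that the analyses will "estimate the effects of the smoking relocation/cessation and resident endorsement interventions compared to the standard program implemented by NYCHA". Neither that section nor the aim-specific, primary-outcome and secondary-outcome sections after it name a multiplicity procedure for the final tests. The flat level of 0.05/3 is therefore the only multiplicity rule in the article, and it stands in the sizing text.

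**The concern.** Under single-step Bonferroni every arm contrast faces 0.0167, whatever the other two show. Once one arm has beaten control, at most two null hypotheses can still be true. The remaining tests could then be run at 0.025 and afterwards at 0.05 without raising the family-wise error above 5%. Holm's procedure uses that slack and Bonferroni does not.

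The slack could matter here. Objectives {7} expects the combined arm to do best. If the standalone arms also work but less strongly, the combined arm tends to be rejected first, and the standalone contrasts are the ones that would benefit. At stake is a moderate amount of power for those later contrasts.

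**Working it through.** **Inputs from the plan.** Three comparisons against one control; two-sided; 80% power; alpha 0.05/3; 16 buildings per arm in all arms (Trial design {8}); detectable effects 0.472, 0.499 and 0.524 SD.

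**Step 1: reproduce the plan's figures.** 0.05/3 = 0.0167, as stated. For the detectable effect, with n subjects per arm in clusters of m = 4,

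SE = sqrt(2 × (1 + (m − 1) × ICC) / n).

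At n = 128 and ICC 0.10, SE = sqrt(2 × 1.3 / 128) = 0.1425. The normal multiplier is 2.394 + 0.842 = 3.236, which gives 0.461 SD. Using the noncentral t with 62 degrees of freedom (32 clusters per arm), the results are 0.472, 0.499 and 0.524 SD at the three ICCs, an exact match.

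**Step 2: does the procedure change the sizing?** No. Holm's first step is also 0.05/3, so the stated detectable effects are the worst-case figures under either method.

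**Step 3: compare the procedures.** I simulated 1,000,000 sets of three normal test statistics per scenario. Equal arms sharing one control give a pairwise correlation of 0.5. The full effect d has non-centrality 3.236, that is, 80% power at 0.0167. Bonferroni rejects when p < 0.0167; Holm uses 0.0167, 0.025 and 0.05 in order.

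| True effects | Contrast | Bonferroni | Holm |
|---|---|---|---|
| none | any false rejection | 4.4% | 4.4% |
| d, d, d | each | 80% | 86.5% |
| d, d, d | all three | 61% | 77% |
| d, d, 0 | each effective arm | 80% | 83% |
| d, 0, 0 | the effective arm | 80% | 80% |
| A and B 0.7d, A+B 1.2d | A or B | 45% | 56% |
| A and B d/2, A+B d | A or B | 22% | 30% |
| A and B d/2, A+B d | A+B | 80% | 81% |

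The chance of at least one rejection is the same for both procedures in every scenario (95% for d, d, d; 92% for d, d, 0; 81% for d, 0, 0). In no draw did Bonferroni reject something that Holm did not.

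**Step 4: the 80% baseline.** The plan says "Sampling 16 clusters (buildings) with 4 subjects per cluster (smokers for Aim 1, non-smokers for Aim 2) in each arm, we have 128 subjects per" arm. But 16 × 4 = 64 per arm for each aim, and the match in Step 1 needs 32 clusters of 4 per arm. With 16 clusters of 4, the detectable effects at 0.0167 are 0.685, 0.724 and 0.760 SD (t, 30 degrees of freedom). At ICC 0.10, SE = sqrt(2.6 / 64) = 0.2016, so an effect of 0.472 SD has non-centrality 2.34 and about 48% power (normal approximation). If all three arms have that effect, Holm gives 55% per comparison against 48%, and 38% against 23% for finding all three.

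**Step 5: the factorial route.** The with/without comparison has twice the sample in each group, so an average effect of f × d has non-centrality f × 3.236 × 1.414, tested at 0.05.

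- A and B at d/2 with A+B at d is additive, so f = 0.5: non-centrality 2.29, power about 63%.
- A and B at 0.7d with A+B at 1.2d: the effect of A averages (0.7 + 0.5)/2 = 0.6, so non-centrality 2.75, power about 78%.

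Both exceed what either procedure gives for the standalone arm contrasts in the same scenarios (22% or 30%, and 45% or 56%).

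**The case against.** The strongest reply has four parts.

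- **Bonferroni is valid.** It is correctly computed and openly called conservative. A reader might infer that the plan makes a statistical error here or contradicts itself; the text does not support that. This is a choice between two valid procedures. The reply stands on status, but it does not remove the gain.
- **The level is in the sizing text only.** The analysis sections fix no final procedure, and an analysis plan that is not shown may name one. A reader might infer that the final tests are firmly bound to the flat level; the article does not go that far. It does, however, name one procedure and no alternative.
- **The loss depends on how many arms work.** A reader might infer that the trial loses power throughout. It does not: the first rejection gains nothing, a single effective arm gains nothing, and the favoured combined arm gains under one point in the scenario with standalone arms at half its effect.
- **The factorial tests already address A and B.** A reader might infer that an effective standalone intervention would simply be missed. The planned comparisons at 0.05 on doubled groups have more power for A and B in both weaker-arm scenarios, so the arm-contrast figures overstate the practical loss if read alone.

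It is also too strong to say that power is given up for nothing. Bonferroni comes with simple simultaneous confidence intervals that agree with its decisions, and Holm does not.

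**Conclusion.** The point holds as a minor efficiency improvement. For the three arm-versus-control tests, Holm dominates the stated procedure at the same 5% family-wise error, with no added assumption about dependence. The benefit lies entirely in the second and third rejections: about 6 points per comparison and 15 to 16 points for finding all three when every arm has the full planned effect, about 3 points each with two effective arms, and essentially none with one.

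The percentages rest on normal test statistics, a correlation of 0.5 from the shared control, and the plan's own 80% power at 0.0167. That last assumption does not fit 16 buildings with 4 subjects each per arm. The mismatch is a separate matter, and it affects power far more than the choice between Bonferroni and Holm.

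**What to change.** In Sample Size {14}, and where the arm contrasts are analysed, state that the three arm-versus-control tests use Holm's step-down at a family-wise alpha of 0.05. Keep 0.0167 as the first-step, worst-case sizing level. Report Bonferroni simultaneous intervals alongside, with a note that they may not agree exactly with the Holm decisions. If an analysis plan already names a procedure, align the two documents. Make the change before outcomes are compared by arm.

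The cost is one sentence in each place. No data, sample size or error rate is affected; the only price is the looser match between intervals and test decisions.

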### Primary outcome

1)

Self-reported average number of cigarettes smoked per day and secondhand smoking exposure (hours of secondhand smoke exposure in the building in the past 7 days) will be measured at baseline (in person interview), 3 months (phone interview) and 12 months (in person interview). Salivary cotinine will be measured for 25% of the sample at baseline and at the 12-month follow-up for smokers to evaluate reliability of self-reported smoking behavior in Aim 1 and for non-smokers to evaluate self-reported secondhand smoke exposure in Aim 2.

To examine the intervention group differences in the change of self-reported smoking (Aim 1), we will use GLMRM with identity link, E(Yijkh) = ßh + ßkhtk + ßZij, where Yijkh is an outcome variable (transformed if necessary) for smoking exposure measured at time tk (t0 = 0 for baseline; t1 = 1 for 6 months, 0 else; and t2 = 1 for 1 year, 0 else) from the ith participant of the jth building in the hth arm/group (h = 1, 2, 3, 4). For the reference group of h = 4, ßk4 = 0 for k = 0, 1, 2; so that parameter ßkh (k = 1, 2; h = 1, 2, 3 for intervention arm) indicates the difference in outcome change since baseline between intervention group h and reference group, and ß is a vector of coefficients for the vector of control variables Zij (if any). To examine if effect of treatment A depends on treatment B or vice-versa, we will test null hypothesis ßk1 = ßk2 + ßk3 for all k, which suggests independent effects of treatment A and treatment B and simpler model that E(Yijk) = ß0 + ß1A + ß2B + ßk0tk + ßk1tk A + ßk2tk B + ßZij with dummy variables A and B indicating treatment type. To examine the intervention group differences in the change in hours of secondhand smoke exposure in the building in the past 7 days for non-smokers, we will use GLMRM with log link (Aim 2). Models will be run with and without control variables (if any).

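### The cotinine effect size is in SDs of one-year change, but the SDs that turn it into 55.3 and 0.19 ng/mL are not identified as SDs of change and read most naturally as SDs of level

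*Protocol article*

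**What the plan says.** All the relevant statements are in the Sample Size {14} section of the protocol article.

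- The powered outcome is "the primary outcome (change in salivary cotinine over a year) in Aims 1 and 2".
- The effect is standardised on that outcome: "We calculated effect size as group mean difference in unit of standard deviation (SD) of the outcome".
- For treatment against no treatment, "the group size of 256 may detect effect size of 0.283SD, 0.299SD, 0.312SD at significance level alpha = 0.05", at intra-cluster correlations of 0.1, 0.15 and 0.2.
- The conversion to cotinine units is that "an effect size of 0.283SD would correspond to a mean difference in salivary cotinine between the two intervention groups of 55.3 ng/mL", with a group SD of 195.4 ng/mL for smokers. For non-smokers it gives 0.19 ng/mL with a group SD of 0.672 ng/mL. Both SDs come from one outside study of smokers.
- The smoker benchmark is that "a mean difference in 5 cigarettes smoked per day in the same study was 59.6 ng/mL for smokers". The non-smoker benchmark is a fall of 0.29 ng/mL after smoke-free legislation elsewhere.

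The section then concludes that power is sufficient. It gives no correlation between baseline and 12-month cotinine and no quantity labelled as an SD of change.

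**The concern.** An effect of 0.283 SD of change must be multiplied by the SD of change to give ng/mL. The SDs used are presented with a mean from the outside study. The benchmark from the same study compares cotinine between smoking intensities, which looks like a contrast of levels. On that reading the effect size and the multiplier are on different scales.

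The ng/mL figures are the section's only link between SD units and a meaningful effect, and the sufficient-power sentence is drawn from them. For smokers the margin is narrow: 55.3 against 59.6 ng/mL, about 7% (55.3/59.6 = 0.928). A moderate difference between the two SDs could remove that margin or widen it a good deal.

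**Working it through.** **Inputs from Sample Size {14}.** Detectable effects d = 0.283, 0.299 and 0.312 SD at intra-cluster correlation (ICC) 0.1, 0.15 and 0.2. SDs 195.4 and 0.672 ng/mL. Benchmarks 59.6 and 0.29 ng/mL. **Assumptions, not in the documents:** the SDs are of level, variance is equal at both visits, and the baseline-to-12-month correlation is ρ, shown over a range.

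**1. The plan's own figures reproduce.** 0.283 × 195.4 = 55.3 and 0.283 × 0.672 = 0.190.

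**2. SD of change.** In general SD_change = √(s0² + s1² − 2ρ·s0·s1). With s0 = s1 = s this is s·√(2(1 − ρ)), which equals s at ρ = 0.5. With unequal variances SD_change equals s0 at ρ = s1/(2·s0), for example 0.4 when s1/s0 = 0.8. Allowing for rounding under equal variances, 55.3 fits ρ from 0.499 to 0.501 and 0.19 fits ρ from 0.474 to 0.527.

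**3. 0.283 SD of change in ng/mL, equal variances.**

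| ρ | √(2(1 − ρ)) | Smokers | Non-smokers |
|---|---|---|---|
| 0 | 1.414 | 78.2 | 0.269 |
| 0.3 | 1.183 | 65.4 | 0.225 |
| 0.4 | 1.095 | 60.6 | 0.208 |
| 0.5 | 1.000 | 55.3 | 0.190 |
| 0.6 | 0.894 | 49.5 | 0.170 |
| 0.7 | 0.775 | 42.8 | 0.147 |
| 0.8 | 0.632 | 35.0 | 0.120 |

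**4. Smoker benchmark.** The detectable difference equals 59.6 at ρ = 1 − (59.6/(d × 195.4))²/2. For d = 0.283 this is 1 − (59.6/55.3)²/2 = 0.42; below that the benchmark is exceeded. At ICC 0.2 no argument about scale is needed: the plan's own SD gives 0.312 × 195.4 = 61.0, already above 59.6.

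**5. Non-smoker benchmark.** At d = 0.283 the largest value for ρ ≥ 0 is 0.269, below 0.29, so the comparison stands. At d = 0.312 it would be 0.312 × 0.672 × 1.414 = 0.297 at ρ = 0, which drops to 0.29 by ρ of about 0.04.

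**6. The 0.283 itself.** Using d = (1.960 + 0.842) × √(2 × DE/n) with DE = 1 + 3 × 0.1 = 1.3, n = 256 per group gives 0.282, in line with the stated 0.283. But 16 buildings × 4 participants is 64 per arm and 128 per pooled group in each smoking stratum. With n = 128, d = 0.40, which is 0.40 × 195.4 = 78 ng/mL at the plan's SD. Outcomes {12} and the assessment section {18a} also limit cotinine to 25% of the sample (128 participants in all), which step 6 does not allow for.

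**The case against.** The section never calls 195.4 and 0.672 SDs of level, and the source study is not at hand. A reader might infer that the wrong SD was certainly used. The documents support less: the SD is unidentified, and level is the natural reading.

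A reader might also infer that the figures hold only at a correlation of exactly 0.5. That needs equal variances, and the rounded 0.19 allows 0.47 to 0.53. Nor does anything in the documents place the correlation in the unfavourable range. Between 0.42 and 0.5 the smoker comparison survives at ICC 0.1, and above 0.5 the stated figures are conservative.

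The Primary outcome section defines a parameter that "indicates the difference in outcome change since baseline between intervention group h and reference group", which might seem to confirm a change-score analysis of cotinine. That model is written for self-reported smoking. The section uses cotinine to check self-report, so it does not settle how cotinine would be analysed.

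Finally, the conversion is offered for perspective, and the effect sizes in SD units do not depend on it. That is true, but the sufficient-power sentence follows directly from the ng/mL comparisons, so they carry weight. The step 6 mismatch in counts is the larger problem, but correcting it alone would leave the scale of the ng/mL figures unresolved.

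**Conclusion.** The point holds as a failure to identify the SD, with a conditional numerical consequence. The effect is defined in SDs of one-year change; the multipliers are not shown to be SDs of change; and no correlation links the two scales. If they are level SDs with equal variance, the smoker figure of 55.3 ng/mL could be 65.4 at correlation 0.3 or 35.0 at 0.8, and the comparison with 59.6 fails below about 0.42 at ICC 0.1.

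Two stronger readings are not supported. One is that neither ng/mL figure can be used: at 0.283 SD the non-smoker comparison with 0.29 holds for every correlation of 0 or more, although 0.19 itself remains unsupported. The other is that the scale question by itself shows the trial to be underpowered: the direction of any error depends on an unknown correlation. All the values based on 0.283 also take 256 per pooled group as given, which the stated buildings and participants do not supply, so they describe the plan's calculation and not the power of the trial as designed.

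**What to change.** In Sample Size {14}, state whether 195.4 and 0.672 ng/mL are SDs of level or of one-year change. If they are SDs of change, saying so settles this point. If they are SDs of level, either give the SD of one-year change or state an assumed baseline-to-12-month correlation, with detectable differences over a range such as 0.3 to 0.8. Then restate 55.3 and 0.19 ng/mL and the sufficient-power sentence, and show the result at all three ICC values.

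Make the change together with a recalculation of the effect size from 64 per arm and 128 per pooled group in each smoking stratum and from the 25% cotinine subsample. Otherwise the ng/mL figures would be restated from an unsupported 0.283.

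The cost is rewriting and recalculating one section; the restatement needs no new participants. The downside is that the stated detectable difference may become less favourable.

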## Methods: Participants, Interventions And OutcomesStudy

### Setting {9}

The New York City Housing Authority (NYCHA) is the largest public housing provider in the US with over 500,000 residents across 335 developments throughout the city via conventional public housing, Section 8, and Permanent Affordability Commitment Together (PACT) or Rental Assistance Demonstration (RAD) housing (64). Though NYCHA is unique in its size and organization of buildings, it is characteristic of other public housing settings in that its entire portfolio of buildings and campuses are subject to smoking bans. Additionally, the resident profiles are similar across socioeconomic status and smoking behaviors. For feasibility, this study will be conducted at public housing sites located across two New York City boroughs where public housing is most concentrated: Manhattan and the Bronx. There are a total of 159 developments and 93,012 current dwelling apartments in these two boroughs. Of these, we have restricted the pool of buildings to contain only buildings managed by NYCHA. Further building inclusion/exclusion criteria are detailed below.

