## Interventions

### Explanation For The Choice Of Comparators {6b}

Buildings and study participants assigned to the comparator arm [Arm 4] are recruited and followed over approximately a 12-month period to assess outcomes. No additional programs or services will be delivered to the buildings or residents assigned to this arm beyond standard programs that NYCHA may provide to support the smoke-free mandate. Field staff will document any policy-related signage, activities, or information to which these participants are exposed. We expect and have confirmed that Smoke-Free NYCHA’s liaison program will occur during our period of data collection during which they will conduct programming and activities that support compliance to the smoke-free policy. As such, the buildings enrolled in our ‘Standard NYCHA approach’ are buildings that the Smoke-Free NYCHA team has identified as locations for concentrated efforts of their own smoke-free programming over the course of our data collection period. We will therefore evaluate the impact of this parallel prevention program including a covariate for NYCHA study participation at baseline in the models specified below. We will further allow for an interaction between the NYCHA study participation indicator and the treatment group.

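### The claim of sufficient power for non-smokers rests on a before-after effect of legislation, which is not the between-arm contrast tested here and falls short of the plan's own arm-versus-control detectable difference

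*Protocol article*

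**What the plan says.** The Sample Size section powers the trial on "the primary outcome (change in salivary cotinine over a year) in Aims 1 and 2". It gives detectable effects in SD units at 80% power for two kinds of contrast, each at intra-cluster correlations (ICC) of 0.1, 0.15 and 0.2:

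- with versus without a given treatment (256 per group, alpha 0.05): 0.283, 0.299 and 0.312 SD;
- each intervention arm versus control (128 per arm, alpha 0.0167): 0.472, 0.499 and 0.524 SD.

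Only the smallest of these, 0.283 SD, is converted to cotinine units: "0.19 ng/mL with group SD = 0.672 ng/mL for non-smokers". The section then brings in two benchmarks. One, on five cigarettes a day, applies to smokers. The other is the only one for non-smokers: "In England, following the smoke-free legislation salivary cotinine declined from mean level of 0.36 to 0.07 ng/mL (mean difference 0.29 ng/mL) among non-smokers". From these it concludes: "These findings support that we have sufficient power to estimate the impact of our interventions".

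Other sections describe what is being compared. Setting {9} says of the housing authority that "its entire portfolio of buildings and campuses are subject to smoking bans". Eligibility Criteria {10} reports that the smoke-free policy was extended to marijuana during recruitment, so it was already in force. Under Explanation For The Choice Of Comparators {6b}, the control arm receives nothing "beyond standard programs that NYCHA may provide to support the smoke-free mandate", and the control buildings are ones the authority has singled out for intensive smoke-free activity of its own.

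**The concern.** The English figure is a change over time whose comparator is the absence of legislation. No arm of this trial lacks a ban. The trial asks what compliance support adds to an existing ban, and the article gives no expected between-arm cotinine difference for that question. A change produced by introducing a law has been put where an expected added effect should stand.

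The mismatch matters because, for non-smokers, the step from a detectable difference to sufficient power has no other support. The section also converts only the more favourable contrast to ng/mL. A reader cannot see from the text how the benchmark compares with the arm-versus-control differences, although the hypothesis in Objectives {7}, which sets the combined arm against the standalone arms and the standard approach, depends on arm-level comparisons. If the sufficiency statement stands unqualified, a null cotinine result for non-smokers could be read as adequately powered evidence of no benefit.

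**Working it through.** **Inputs (all from Sample Size {14}).** Group sizes 256 and 128; 4 subjects per building; ICC 0.1 to 0.2; two-sided alpha 0.05 and 0.0167; power 80%; non-smoker SD 0.672 ng/mL; benchmark 0.36 − 0.07 = 0.29 ng/mL. The subject counts are taken as stated.

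**Step 1. Reproduce the plan's detectable effects.** With design effect 1 + (4 − 1) × ICC,

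SE in SD units = √(2 × [1 + 3 × ICC] / n).

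| Contrast | ICC | SE | Recomputed | Stated |
|---|---|---|---|---|
| Pooled, n = 256 | 0.1 | 0.1008 | 0.283 | 0.283 |
| | 0.15 | 0.1064 | 0.299 | 0.299 |
| | 0.2 | 0.1118 | 0.314 | 0.312 |
| Arm vs control, n = 128 | 0.1 | 0.1425 | 0.472 | 0.472 |
| | 0.15 | 0.1505 | 0.498 | 0.499 |
| | 0.2 | 0.1581 | 0.524 | 0.524 |

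The recomputed values are noncentral-t solutions, on subject degrees of freedom for the pooled rows and cluster degrees of freedom for the arm rows. The stated figures reproduce, and 0.29 ng/mL is nowhere among their inputs.

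**Step 2. Convert to ng/mL and compare with the benchmark.** Multiply the stated effect by 0.672, then divide by 0.29.

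| Contrast | ICC | ng/mL | Share of 0.29 |
|---|---|---|---|
| Pooled | 0.1 | 0.283 × 0.672 = 0.190 | 66% |
| | 0.15 | 0.299 × 0.672 = 0.201 | 69% |
| | 0.2 | 0.312 × 0.672 = 0.210 | 72% |
| Arm vs control | 0.1 | 0.472 × 0.672 = 0.317 | 109% |
| | 0.15 | 0.499 × 0.672 = 0.335 | 116% |
| | 0.2 | 0.524 × 0.672 = 0.352 | 121% |

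**Step 3. Power if the whole 0.29 appeared between arms.** The effect is 0.29 / 0.672 = 0.432 SD. Noncentrality is the effect divided by the SE, with degrees of freedom on clusters (n/4 per side).

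- Pooled (126 df, critical value 1.979): noncentrality 4.28 at ICC 0.1 and 3.86 at ICC 0.2; power 99% and 97%.
- Arm versus control (62 df, critical value 2.460): noncentrality 3.03 and 2.73; power 71% and 61%.

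**Step 4. Illustration only.** The documents do not say what part of 0.29 compliance support might add, so the shares below are assumptions. Each range runs from ICC 0.2 to ICC 0.1.

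| Assumed share of 0.29 | Pooled power | Arm-versus-control power |
|---|---|---|
| 75% | 82 to 89% | 35 to 43% |
| 50% | 48 to 57% | 14 to 18% |
| 25% | 16 to 19% | 4 to 5% |

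**The case against.** **The figure is illustrative.** It is introduced to give perspective, and deleting it changes no sample size, alpha or detectable effect. This stands, and Step 1 confirms it. A reader might infer that the power calculation itself is built on 0.29 ng/mL; it is not. What depends on the figure, for non-smokers, is the closing statement that power is sufficient.

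**A ban on paper is not a ban in effect.** Background And Rationale {6a} describes housing policies that were widely broken: about half of residents or guests in violation in one study, almost 20% frequently exposed in another, and later studies with no change or a 33% rise in environmental markers. Compliance support might then deliver much of what an effective ban would. This also stands. A reader might infer that the ban's effect is shared by all arms and so drops out of every comparison; the article's own account of poor compliance does not support that. It makes 0.29 a conceivable upper reference, but not an expected difference, and the Sample Size section does not argue the case.

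**The post-legislation level.** Because 0.07 ng/mL lies below 0.19, a reader might infer that even eliminating exposure could not yield the detectable difference. Nothing in the article places these residents at 0.07. The background section reports raised cotinine in non-smokers in multiunit housing, and with change over a year as the outcome, a rise among controls could also create a difference. The floor argument is not relied on.

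**Other matters weigh more.** The primary-outcome model for Aim 2 uses self-reported hours of exposure, with cotinine as a check on self-report. Also, 16 buildings of 4 non-smokers make 64 per arm, not 128, and saliva comes from 25% of participants. These are separate points. The last two would lower the power shown here, and the Sample Size section and Outcomes {12} both still name cotinine as a primary outcome.

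**Conclusion.** The point holds for the sufficiency statement on non-smokers and for nothing wider. A before-after legislation effect has been used as though it were a plausible between-arm effect, in a trial where all arms are already under a ban and control buildings receive smoke-free programming as well.

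For the arm-versus-control contrasts the statement fails on its own benchmark: the detectable difference exceeds 0.29 ng/mL at every stated ICC, and power at the full 0.29 is 61 to 71% rather than 80%. For the pooled contrast the benchmark clears the detectable difference, but only if compliance support adds about two-thirds or more of the whole legislation effect on top of the existing ban, which the article does not argue.

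These results rest on the section's own counts, SD and ICC range. They do not show that the trial is underpowered for its true effect, which cannot be derived from the documents. The partial-share powers in Step 4 only show how quickly power falls.

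**What to change.** In Sample Size {14}:

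1. Remove the English legislation figure as support for power, or label it an upper reference for a different contrast (before versus after a law).
2. Give the non-smoker detectable differences in ng/mL for both contrasts: 0.19 to 0.21 pooled and 0.317 to 0.352 arm versus control, on the stated counts.
3. Express both as relative reductions from the baseline cotinine mean of non-smokers, with the observed SD, using the samples already being collected, pooled across arms and summarised without arm labels.
4. Withdraw the sufficiency statement for the Aim 2 arm-versus-control cotinine contrasts. For the pooled contrast, qualify it by stating the size of added effect that it requires.

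The cost is a rewritten paragraph and one pooled, arm-blind summary of baseline data. The design does not change. The downside is that the stated power for Aim 2 becomes less favourable.
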